[figure not shown]

## 1.1 Project summary

NHS Test Beds aim to assess the value of new technologies to healthcare delivery in the UK and have emerged in response to pressures facing the NHS. A test bed involves frontline health and care workers pioneering the use of novel technologies and ways of working to help patients stay well and monitor their conditions themselves at home. One of these Test Beds aims to improve the care of patients with diabetes, heart failure and chronic obstructive pulmonary disease (COPD) by combining clinical audits, population management software, structured training of primary care teams and a patient monitoring and coaching telephone service over a 12-month period in a single Clinical Commissioning Group (CCG). Since similar complex interventions have failed to demonstrate effects because of poor implementation/adherence, this qualitative study will evaluate the implementation of the Test Bed by exploring the extent to which the programme is acceptable to health care professionals and the extent to which professionals’ behaviour/s is/are in line with that intended by the programme leaders.

Observation and longitudinal interviewing of key stakeholders (NHS professionals and other staff) will explore these issues in-depth to identify barriers and facilitators to implementing the Test Bed, and explore if, and how, these factors change during the Test Bed. With participants’ consent, qualitative interviews will be audio-recorded and transcribed by a University-approved supplier. The recording device is not encrypted, but the audio file will be transferred by the researcher to a secure server at the University of Manchester and the original file will be deleted from the audio device. Field notes will be made during observations. NVivo software will support the thematic analysis of interview transcripts, field notes and reflections. Documentary analysis will enrich the thematic analysis to provide an in-depth description of events.

Ethical approval will be obtained through the University of Manchester Research Ethics Committee (UREC) If the decision is taken to roll out the Test Bed, the results of this study will inform its implementation beyond the CCG.

### Study summary at a glance

| Study Title | Heywood Middleton and Rochdale Long Term Conditions NHS Test Bed: A service evaluation of implementation and impact |
| --- | --- |
| Short title | HMR NHS Test Bed - qualitative evaluation (version 1) |
| Study Design | Qualitative process evaluation using observations and interviews |
| Study Participants | Staff at GP practices, the CCG and MSD involved in implementing the Test Bed |
| Planned Size of Sample (if applicable) | N/A |
| Follow up duration (if applicable) | N/A |
| Planned Study Period | 18 months |
| Research Question/Aim(s) | The aim of the study is to evaluate the implementation of the Heywood Middleton and Rochdale Long Term Conditions NHS Test Bed package. The study will achieve this by addressing the following objectives:   - To what extent is the Test Bed programme acceptable to health care professionals? - To what extent is/are the behaviour/s of health care professionals in line with that intended by the programme leaders? |

## Rationale & background information

The burden of disease is shifting to long-term conditions, and there is significant interest in the development of interventions that can improve care for these conditions [1]. Preferably, these interventions need to meet the ‘triple aim’ of improving outcomes, reducing costs, and enhancing patient experience, although at a minimum there is a need to develop interventions that can reduce cost without compromising outcomes and experience [2].

A variety of interventions have been tested, including:

- Improvements in the quality of care for long-term conditions through adoption of clinical guidelines and other standard quality improvement methods [3, 4].
- Use of risk stratification models, linked to clinical interventions like case management [5, 6].
- Telehealth, using a variety of models including in-home sensors and more active remote monitoring of long-term conditions [7-9].

Evidence of effectiveness is variable for all these approaches, and it is unclear what interventions are effective, the populations they are effective in, or the contexts in which they can best achieve change.

There is also increasing consensus that attempting to significantly reduce care costs requires ‘large scale transformations’ rather than the delivery of discrete interventions [10].

The NHS Five Year Forward View first proposed new NHS Test Beds, which were designed to assess the value of new technologies. A test bed was described as an area where:

‘Frontline health and care workers …. will pioneer and evaluate the use of novel combinations of interconnected devices such as wearable monitors, data analysis and ways of working which will help patients stay well and monitor their conditions themselves at home’

In 2016, the NHS announced the NHS Test Bed Programme (<https://www.england.nhs.uk/ourwork/innovation/test-beds/>). Heywood, Middleton and Rochdale Clinical Commissioning Group (HMR CCG) successfully led a submission to the NHS England Test Bed programme looking to pioneer and evaluate the ‘use of novel combinations’ of interconnected innovations to improve patient outcomes at the same or lower cost, when compared to routine care (<https://www.england.nhs.uk/wp-content/uploads/2015/03/test-bed-prospectus.pdf>). The HMR CCG Test Bed is designed to improve how GP practices manage patients with diabetes, heart failure and COPD, and has three core components:

1. Clinical audit and population management software for primary care healthcare professionals (called ‘MSDi’)
2. A structured 12-month training programme that ‘upskills’ primary care teams (called ‘Evidence into Practice’)
3. Remote telehealth monitoring service and coaching for up to 1500 patients with Heart Failure or COPD (called ‘Closercare’)

The combination of these interventions, delivered over a 12-month period in a single CCG, is expected to deliver greater impact on health care utilisation (especially hospital admissions) than the individual components alone.

The combination of components in the Test Bed has the characteristics of a ‘complex intervention’ (as defined by the MRC) [11], which are by their nature difficult to implement, as they require changes in service delivery and organisation to be undertaken by professionals and patients in a relatively short period of time [11-13]. There are many examples in the literature of similar health care models which have failed to demonstrate effects because of poor implementation or adherence [14]. It is therefore important to qualitatively evaluate the implementation of the Test Bed under investigation to understand how the programme’s outcomes may have been affected by what was implemented. Furthermore, any roll out to other sites will require guidance on how to implement this type of intervention in such a way as to increase chances of success.

## 1.4 Study goals and objectives

The aim of the study is to evaluate the implementation of the Heywood Middleton and Rochdale Long Term Conditions NHS Test Bed package. The study will achieve this by addressing the following objectives:

- To what extent is the Test Bed programme acceptable to health care professionals?
- To what extent is/are the behaviour/s of health care professionals in line with that intended by the programme leaders?

## 1.5 Study Design and Methodology

The qualitative study is a process evaluation using observations and interviews with a range of staff involved in the implementation of the Test Bed within HMR CCG. The research population will consist of members of staff at HMR CCG, MSD and GP practices within the CCG. HMR CCG is one of the most deprived areas in England, with high prevalence of diabetes, heart failure and COPD. According to local data, two per cent of patients account for 17% of the healthcare spend. We will select eight GP practices in which to conduct the qualitative research. This number is a compromise between the breadth required to capture sufficient variation and the depth needed for detailed exploration. The research sites will be purposively sampled based on practice size and ensuring that all change managers are included.

The MRC defines a process evaluation as:

‘A study which aims to understand the functioning of an intervention, by examining implementation, mechanisms of impact, and contextual factors. Process evaluation is complementary to, but not a substitute for, high quality outcomes evaluation’ [15].

Implementation is defined as: ‘the process through which interventions are delivered, and what is delivered in practice. Key dimensions of implementation include: implementation process (the structures, resources and mechanisms through which delivery is achieved); fidelity (the consistency of what is implemented with the planned intervention); adaptations (alterations made to an intervention in order to achieve better contextual fit); dose (how much intervention is delivered); reach (the extent to which a target audience comes into contact with the intervention)’ [15].

To assess implementation, we will use a combination of observation and interviews. We will conduct up to 90 interviews in total. We will interview professionals (n=4-5) at each practice early on in the evaluation and interview these same professionals towards the end of the process (up to 80 interviews in total). In addition, we will interview staff from MSD and HMR CCG (e.g. members of the Change Team who are involved in staff training and supporting practice staff more generally). Qualitative research interviews will be conducted either face to face at participants’ places of work, or by telephone, and will last up to 1 hour; interviews will take place at participants’ convenience. Potential interview participants within GP practices will be selected by convenience, pragmatic sampling. Potential interview participants outside GP practices (staff at CCG and MSD) will be purposively sampled based on their involvement in setting up the Test Bed. Purposive sampling (based on emerging themes) will be used latterly in response to initial recruitment, data collection and data analysis.

We will also observe professionals in each of the study sites and members of staff at HMR CCG and MSD in meetings/workshops/sessions that focus on the implementation of the Test Bed. Observations will be identified based on whether or not meetings/sessions/workshops focus on the Test Bed. Potential participants attending these meetings/sessions/workshops will therefore be purposively sampled. Purposive sampling (based on emerging themes) will be used subsequently in response to initial recruitment, data collection and data analysis.

Data collection and analysis will be undertaken concurrently. In addition to notes and reflections on observations and interview transcripts, we will use documentary analysis to provide ‘thick description’ of events [16]. Analysis will initially involve coding transcripts using NVivo software and identifying themes. We will use the programme’s intended mechanisms of change to help inform our understanding of the data and focus for data collection. We will not use a specific theoretical framework, but will adopt a sufficiently broad approach to ensure that we do not miss important issues or factors by restricting analysis in too narrow a fashion.

Individuals outside the research team will make the first approach to potential participants; the research team will not contact potential participants in the first instance; we will only contact potential participants that have contacted us and provided their contact details. All potential interview participants will be asked to contact the research team if they are interested in taking part in the study)’. Potential participants for observations will be able to object/agree to being observed by contacting the chair, who will inform the research team, or telling the researcher face to face immediately before the proposed observation. Individuals outside the research team will send reminder emails to potential participants. Written consent will be obtained from interview participants and verbal consent will be obtained for observations (see1.15 Ethical and Regulatory Considerations).

Inclusion criteria: Any staff in the selected GP practices or employed by HMR CCG or MSD involved in the implementation/delivery of the Test Bed will be eligible to participate in the qualitative interviews. Similarly, any participants outside and within these practices attending meetings/workshops/sessions that are relevant to the study’s aims and objectives will be eligible for observations.

Exclusion criteria: Staff at practices, CCG and MSD without a strong verbal command of the English language will not be eligible to participate in the study.

Withdrawal criteria: participants will be able to withdraw from the study without giving a reason. Should participants wish, their data can be withdrawn and destroyed prior to publication of results.

Ethical and site approvals will be submitted in May/Jun 2017. The empirical research will commence following approval and finish by 31^st^ October 2018. The study’s schedule is outlined in 1.12 Duration of the Project.

## 1.6 Safety Considerations

For staff observations, the main burden for participants will be the intrusion of having events observed by a researcher. To minimise this, the researcher will be flexible to the times of scheduled events (e.g. practice meetings and training sessions) when conducting observations. Participants will be informed about the research beforehand and able to decline to participate. If participants object to observation, the event will not be observed.

For staff interviews, the main burden for participants will be giving time to be interviewed. Given that busy staff might find it hard to make time for interviews, researchers will be flexible in finding a time and place that is convenient for participants, offer telephone interviews, and remind potential participants that their participation is voluntary.

While the risk is low, we will follow the University’s Lone working policy and risk assessment for off-site work in the UK to ensure our safety. The Lone Working policy includes details of a 'buddy system' (including contingent arrangements for annual leave, bereavement and sickness) and the escalation process. Before travelling to each site, the lone worker will have informed the buddy of the location, date, and time of the interview/observation. Anticipated times of arrival and return will be agreed and the lone worker will contact the buddy at these times. Where the lone worker fails to adhere to agreed arrangements, the buddy will first attempt to contact the lone worker. Where this is unsuccessful, the buddy will escalate to University Security who will advise if police involvement is needed.

## 1.7 Follow-Up

Routine follow-up of participants is not planned for this study because the topic is non-sensitive.

##

## 1.8 Data Management

Data generated by the study will be managed in accordance with the University's Data Protection Policy, Records Management Policy and Information Security Policy.

Manual personal data will be stored in a locked cabinet, in an office that is locked when unattended, at the University of Manchester. Confidential waste will be destroyed in accordance with the relevant University procedures. Access to the information will be limited to the study staff and investigators and relevant regulatory authorities.

Digital data will be encrypted, password-protected and stored on a secure RDS server at the University of Manchester; the login credentials of investigators are required to access the server, thereby restricting access only to those members of the research team that need it ([name] and [name]). The University of Manchester’s Research Data Management Service (RDMS) provides robust, managed, secure, replicated storage, and allows researchers to store, manage and curate their data. All electronic data will be stored and automatically backed up daily on secure University of Manchester RDS server, allowing data to be recovered in the event of an incident. Files stored on this service can be considered secure. For example, files corrupted or accidentally deleted can be recovered for up to 35 days.

Personal identifiable data such as participants’ names and work details (telephone numbers, email addresses) will be stored as password-protected digital files on the secure RDS server. To enable these data to be stored separately to interview and observation data, each participant in the study will be assigned an identification number; the anonymisation key linking participants to the interview/observation data will be stored in a separate location.

Whenever possible, personal data will be encrypted and password-protected during electronic transfer. In the following situations, it will not be possible to encrypt personal data during electronic transfer data: 1) Digital audio files will be wire-transferred from an audio-recording device to the secure University RDS; 2) Digital audio files will be uploaded to the secure website of the University-approved transcription service from the secure University RDS; 3) Verbatim transcripts will be downloaded from the secure website of the University-approved transcription service to the secure University RDS. The transcription company is based in the UK and managed through a secure website, and has signed a confidentiality agreement with the University to ensure all personal or sensitive data are protected and stored securely during and after transcription has occurred.

Data from interviews, documents and observations will be analysed together using NVivo software. This will take place at the University of Manchester and will be conducted by the research team comprising members of staff at the University of Manchester. All the data will be stored on the University's secure RDS server and team members will have access to it.

Members of the qualitative research team conducting data collection and analysis will therefore have access to personal data during the study. Study data and material may also be looked at by individuals from the University of Manchester, from regulatory authorities or from the NHS Trust, for monitoring and auditing purposes, and this may well include access to personal information. When the primary buddy ([name]/[name]) is unavailable (sickness, bereavement, annual leave), the ‘contingent’ buddy will need to have access to interview/observation details (participants’ names, interview/observation location, start and end times) in order to perform this role. [name] will perform the ‘contingent’ buddy role in the first instance. If [name] is unavailable, a member of staff at the University of Manchester will perform this role.

The University's Data Protection Policy, Records Management Policy and Information Security Policy will inform arrangements for storing research data after the study has ended. Research data generated by the study will be stored for 10 years. Manual data will be stored physically in locked filing cabinets at the University of Manchester; digital data will be archived using the RDMS. Consent forms will be retained as essential documents for 10 years, but items such as contact details will be deleted as soon as they are no longer needed. No other identifiable manual data will be stored after the study has ended. Digital audio files will be stored for a minimum of 5 years (maximum 10) before being destroyed; anonymised copies of digital transcripts will be stored for 10 years on the RDS server. All other digital data that will be stored/accessible via the RDMS service after the study will be anonymised (e.g. transcripts, field notes). The anonymisation key will be archived and destroyed at the same time as digital audio files.

In order to perform her data custodian role beyond the study, only [name] will have access to archived digital and manual data. The University of Manchester will cover the costs of archiving. Archiving arrangements will be water-, pest- and fire-proof. Archived data will be destroyed in accordance with the relevant University policies.

Data generated by the study will not be shared for other research and/or teaching purposes.

## 1.9 Quality Assurance

The study will be subject to the audit and monitoring regime of the University of Manchester.

## 1.10 Expected Outcomes of the Study

The results will inform any roll out of the Test Bed beyond HMR CCG; however, the concurrent quantitative analysis will determine the impact of the Test Bed and therefore inform any decision about whether or not to roll it out beyond HMR CCG. The qualitative data will be considered after the results of the quantitative analysis are known in order to aid interpretation of results.

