## 1.11 Dissemination of Results and Publication Policy

The results of the study will be published as a full journal paper in an academic peer reviewed journal; a member of the research team will take the lead in publications. All study team members who make a substantive contribution to reading and writing the final report will be granted authorship on the final study report*.* Funders and participants will be acknowledged in publications. Interim and final reports will also be provided to those funding the research and the Test Bed Programme National Evaluation. The final report will be sent to all participants after the study has ended.

The funders will have no role in the collection, management, analysis and interpretation of data; writing of the report; or the decision to submit the report for publication.

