## 2.2 Other support for the Project

### 2.2.1 Collaboration with other scientists or research institutions

The study team does not plan to collaborate with other research institutions. However, it will provide a summary of interim findings to the team coordinating the evaluation of the Test Beds programme nationally.

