### 2.2.2 Links to other projects

This study is linked to a quantitative evaluation of the NHS HMR Test Bed led by [name] (Professor of Health Economics, University of Manchester). The data collection process is intended to inform interpretation of the quantitative findings.

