## Study Flow Chart

| **Stage** | **May-17** | **Jun-17** | **Jul-17** | **Aug-17** | **Sep-17** | **Oct-17** | **Nov-17** | **Dec-17** | **Jan-18** | **Feb-18** | **Mar-18** | **Apr-18** | **May-18** | **Jun-18** | **Jul-18** | **Aug-18** | **Sep-18** | **Oct-18** |
| --- | --- | --- | --- | --- | --- | --- | --- | --- | --- | --- | --- | --- | --- | --- | --- | --- | --- | --- |
| UREC application |  |  |  |  |  |  |  |  |  |  |  |  |  |  |  |  |  |  |
| Sponsor Review |  |  |  |  |  |  |  |  |  |  |  |  |  |  |  |  |  |  |
| UREC approval |  |  |  |  |  |  |  |  |  |  |  |  |  |  |  |  |  |  |
| Sampling and recruitment |  |  |  |  |  |  |  |  |  |  |  |  |  |  |  |  |  |  |
| Observations |  |  |  |  |  |  |  |  |  |  |  |  |  |  |  |  |  |  |
| Initial interviews |  |  |  |  |  |  |  |  |  |  |  |  |  |  |  |  |  |  |
| Data analysis 1 |  |  |  |  |  |  |  |  |  |  |  |  |  |  |  |  |  |  |
| Interim report |  |  |  |  |  |  |  |  |  |  |  |  |  |  |  |  |  |  |
| Sampling and recruitment |  |  |  |  |  |  |  |  |  |  |  |  |  |  |  |  |  |  |
| Follow-up interviews |  |  |  |  |  |  |  |  |  |  |  |  |  |  |  |  |  |  |
| Data analysis 2 |  |  |  |  |  |  |  |  |  |  |  |  |  |  |  |  |  |  |
| Final report |  |  |  |  |  |  |  |  |  |  |  |  |  |  |  |  |  |  |
| Publication |  |  |  |  |  |  |  |  |  |  |  |  |  |  |  |  |  |  |

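### The protocol does not require the final acceptability and fidelity conclusions to be fixed before the impact result is seen, and sections 1.10 and 1.5 leave the order of analysis unclear

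*Protocol*

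**What the plan says.** Four parts of the protocol bear on when the qualitative data are analysed and for what purpose.

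- **Section 1.10** gives the order of the two strands: "The qualitative data will be considered after the results of the quantitative analysis are known in order to aid interpretation of results". The same section calls the quantitative analysis concurrent and leaves the roll-out decision to it.
- **Section 1.5** says: "Data collection and analysis will be undertaken concurrently". Transcripts are coded and themes identified as the work proceeds, and the themes feed back into recruitment: "Purposive sampling (based on emerging themes) will be used latterly in response to initial recruitment, data collection and data analysis". No specific theoretical framework is adopted. The programme's intended mechanisms of change help to guide the reading of the data.
- **The Study Flow Chart** lists "Data analysis 1" and an interim report above the follow-up interviews, a second data analysis and the final report.
- **The purpose** is explanatory as well as descriptive. The rationale section wants the evaluation "to understand how the programme’s outcomes may have been affected by what was implemented", and section 2.2.2 adds: "The data collection process is intended to inform interpretation of the quantitative findings".

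**The concern.** A process evaluation helps to explain an outcome most convincingly when its judgements about delivery were reached without knowledge of that outcome. If the impact result is null and the analysts know it, barriers are easier to notice and weight. If it is favourable, facilitators are. The rationale section already offers a ready account of a null result, since it notes that comparable programmes failed because of poor implementation or adherence.

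At stake is the ability to tell a programme that was poorly delivered from one that was delivered but did not work. Section 1.10 expects the findings to inform any roll-out, and guidance on how to implement the Test Bed elsewhere is weaker if the fidelity judgement was itself influenced by the result.

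**Working it through.** No formula applies to the order of the analyses, so the check sets the sections side by side. Simple counts show how much of the material is exposed.

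**1. Does 1.10 describe the thematic analysis or a later integration step?** Read alone, it places consideration of the qualitative data after the impact result. Read with 1.5 and the flow chart, it more naturally describes integration, because coding is already under way during fieldwork. The protocol uses no term that separates the two steps, so both readings remain open.

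**2. Is anything fixed before the result is known?** Sections 1.5, 1.8, 1.10, 1.11, 1.14, 2.2.1 and 2.2.2 and the flow chart contain no statement that themes are dated or closed before disclosure, and none that the qualitative analysts are kept unaware of the quantitative results. The quantitative evaluation is linked and led from the same university (2.2.2), so nothing in the design keeps the results apart.

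**3. Could the result arrive before the second analysis round closes?** The protocol gives no date for the quantitative result. It gives an end date for the empirical research, 31 October 2018 (1.5 and 1.12), and a 12-month programme, but no programme start date. The month shading of the flow chart cannot be read in the text available. The order is undetermined, and the protocol has no rule that settles it.

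**4. Which material is exposed?** From 1.5: 8 practices, 4 to 5 professionals each, the same people interviewed twice.

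- Per wave: 8 × 4 = 32 to 8 × 5 = 40 interviews.
- Both waves: 2 × 32 = 64 to 2 × 40 = 80, which reproduces the protocol's ceiling of 80.
- Remainder of the overall ceiling of 90: 90 − 80 = 10 for staff at the CCG and MSD, if all 80 practice interviews take place.

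The follow-up wave, half of the practice interviews, comes after the first analysis round and so enters at the second. The final fidelity judgement depends on it, because behaviour late in the programme is reported there.

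**5. How much room does the analysis leave?** Coding is open. The intended mechanisms of change give a partial anchor, but no rule is stated for turning the data into a judgement of acceptability or fidelity. Section 1.8 has interviews, documents and observations analysed together, and no first-round theme set is kept as a separate, unrevised record.

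**The case against.** A reader might infer from 1.10 that the qualitative data are left untouched until the impact result is known. The protocol does not support that. Coding runs during fieldwork, a first analysis round is scheduled, and interim output goes outside the team. Section 1.11 says: "Interim and final reports will also be provided to those funding the research and the Test Bed Programme National Evaluation". Section 2.2.1 says of the study team that "it will provide a summary of interim findings to the team coordinating the evaluation of the Test Beds programme nationally". Themes that have been reported in this way leave a trace. This part of the objection stands.

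A reader might also infer that the study is unable to give an independent explanation of the outcome. That is too strong. Early interviews are held near the start, so what was said in them cannot be changed by a later result. The two objectives, acceptability and consistency of behaviour with programme intent, are not defined by the impact outcome. Interpreting a known result with qualitative findings is a declared and legitimate aim (2.2.2).

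Third, it can be said that the order of events is unknown and that nothing shows the team would receive impact results during coding. That is correct, and it limits the point to an absent safeguard. It does not remove the point: early themes and an interim report do not protect the final judgement, which draws on the follow-up interviews and the second analysis round.

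Finally, one might try to express the risk as a chance of spurious agreement between themes and outcomes across the eight practices. The protocol plans no practice-level matching of that kind and gives neither a number of themes nor practice-level outcomes. Any such figure would rest on invented inputs.

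**Conclusion.** The point holds as an ambiguity combined with a missing safeguard. Sections 1.10 and 1.5 need to be reconciled, and the final acceptability and fidelity conclusions are not assured of being independent of the impact result.

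The exposure lies in the second analysis round and the 32 to 40 follow-up practice interviews that feed it. First-wave themes and the interim report may predate the result, although the protocol does not confirm this. The amount of bias cannot be estimated from the document.

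The conclusion assumes that the impact result could reach the qualitative team before the second round closes, which the protocol neither states nor prevents. If the result comes later, the practical risk is small and only the wording needs repair. This is an inexpensive improvement and not a reason to hold up the study.

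**What to change.** Replace the sentence in 1.10 with wording such as:

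> Coding of both interview waves and a dated summary of acceptability and fidelity findings will be completed and locked before the qualitative team sees any quantitative impact result. The qualitative findings will then be used to help interpret the quantitative results, and this integration will be reported separately as post-result interpretation.

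This settles the reading of 1.10 against 1.5, leaves concurrent coding and theme-led sampling as they are, and keeps the purpose declared in 2.2.2.

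The cost is one protocol sentence, one dated file, and a qualitative team that stays unaware of the impact result until the second analysis round closes.

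The change should not be extended to linking practice-level summaries to the quantitative evaluation. Section 1.8 rules out sharing the data for other research, and 1.15.1 keeps details of participation within the research team and promises confidentiality to the practices. The safeguard works without such a link.
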